**c. Pilot evaluation.** As a general overview of activities: each participant will attend two in-person visits (baseline, 2 months) at one of three EHS sites. Each in-person visit will take approximately 2 hours. Bilingual-bicultural staff will conduct computer assisted personal interviews (CAPI) to administer fully structured, objective questionnaires and enter information directly into the secure, web-based data management system, Qualtrics. Dental examination screening data will be entered directly into REDCap in an eCRF adapted from the ASTDD Basic Screening Survey. The smart powered TB and TP pump will be provided at the baseline visit, and study staff will instruct parents/caregivers on their use. Staff will also provide fluoride TP tubes to families to reduce the possibility of other family members using the TP pump. Participants will be asked to bring the TP pump with them to the 2-month follow-up visit; staff will weigh the pump to ascertain this toothbrushing adherence measure. Depending on the information gathered from the qualitative phase of this UH2 study, parents/caregivers will be instructed to regularly (e.g.,

twice a week) download (sync) data from the smart powered TB to their phone app which then is uploaded to the manufacturer's web-based database (cloud) regarding the length of time the TB was used on the child.

Subject participation for this pilot study will take approximately 2-3 months to complete.

If more than one child in the household is eligible to participate in the study, the oldest eligible child will be the index child. The parent/caregiver will be instructed to have each study-eligible child use his/her own smart TB for the duration of the study, but only the index child's TB will be synced to the smart phone app. Each child participant's TB will have a label with his/her name put on the handle along with customized individual stickers to avoid confusion. Participants will be asked not to allow other people to use the study child's smart TB for the duration of the study.

---

## **5 STUDY ENROLLMENT AND WITHDRAWAL**

### **5.1 Subject Inclusion Criteria**

To be eligible to participate in this study, a parent/caregiver must meet all of the following criteria:

- Provide signed and dated informed consent form in English or Spanish.
- Agree to comply with all study procedures and be available for the duration of the study visit.
- Male or female, aged 18 and older.
- Speak, read, and write either English or Spanish.
- Be a parent or caregiver of a child at least 6 months old but less than 3.5 years (42 months), with at least 2 fully erupted teeth and enrolled in, or waitlisted for, one of the three participating Los Angeles County EHS home visit programs.
- Not be planning to move residence for the next 6 months outside the greater Los Angeles area.
- Own a smartphone with the Google Play or iTunes store and be willing to download the smart powered TB app
- Be willing to be contacted via text-messaging (SMS) for study related notifications, such as incentives earned or reminders to sync the TB

### **5.2 Subject Exclusion Criteria**

A child who meets any of the following criteria will be excluded from participation in this study:

- Known allergic reaction to components of the study product(s).
- Uncooperative or behaviorally unsuited (assessed during a TB prophylaxis at the initial baseline study visit).
- A sibling of a child already enrolled in the study (the family's oldest child in the eligible age range will be the study child).
- Enrolled in foster care.
- Anything else that would place him/her at increased health risk or preclude the individual's full compliance with or completion of the study.

### **5.3 Strategies for Recruitment and Retention**

Using the standardized Recruitment Script, research study personnel will contact EHS home visit program families to determine interest in study participation. This outreach may

occur at the EHS center, during EHS monthly parent meetings, or via telephone calls to interested parents/caregivers who contacted study staff.

Mailings and flyers with study recruitment information may also be sent out or posted in the EHS facilities. The monthly EHS newsletter may also include an invitation to participate in the pilot.

EHS families who have participated in previous BEECON surveys or interviews may also be contacted by study personnel to inquire about their interest in participating in the pilot.

## **5.4 Treatment Assignment Procedures**

Because study participant retention is essential, research staff may attempt to contact participating parents/caregivers via postcard mailings and phone calls between the two visits throughout the study to update contact information, in addition to reminding them of the follow-up appointment. Additionally, the parents/caregivers may receive text reminders to sync the smart powered TB to their smartphone app and/or messages about the importance of an early dental visit, serving as other reminders of the project. Finally, all study participants will be sent weekly SMS text messages with preventive behavior reminders, twice daily toothbrushing adherence status per smart TB data, and the incentive earned if assigned to an incentive group.

Each participant will receive a \$30 gift card at the end of the baseline visit, and another \$30 gift card at the end of the 2-month follow-up visit as compensation for their time. Participants will also be eligible to receive additional gift cards for syncing the smart powered TB app data throughout the study period, paid at the 2-month follow-up visit. To encourage participants to bring the TP pump for weighing with them to the 2-month follow-up visit, they will be informed that they will be given the gift cards, a new TP pump, and replacement brush heads only if they return the TP pump.

## **5.5 Treatment Assignment Procedures**

Based on multiple discussions with EHS staff, a trial with different programs will need to demonstrate fairness in a transparent way to the parents/caregivers. Thus, during the explanation of the study to the participant, randomization and the rewards program will be explained with a teachback method. Stratified permuted block randomization will be used to assign participating dyads to a study arm, stratifying on EHS site and varying block size to reduce probability of guessing the next assignment. Once eligibility is confirmed and informed consent is documented, the project coordinator will open a sealed opaque envelope with the participant's study ID number to reveal group assignment for the parent/caregiver-child dyad.

### **5.5.1 Masking Procedures (if applicable)**

Independent dental examiners, PIs, and EHS home visitor staff (one per EHS site) will be blinded to participants' group assignment and participants will be told those staff members

cannot answer any incentive questions and they should not mention the incentive program to them. The researcher providing the incentive gift cards will not be blinded. Dental screenings will precede monetary incentive payment.

## **5.6 Subject Withdrawal**

Participants may withdraw voluntarily from the study at any time.

### **5.6.1 *Reasons for Withdrawal***

Participants may decide not to answer any CAPI item or not to participate in the study further at any time without penalty.

Participants are free to withdraw from participation in the study at any time upon request, for any reason, without penalty or loss of benefits as a member of the EHS program. This may occur due to discomfort with questions or practical concerns that limit the time available (e.g., pressing employment schedule or child care needs).

An investigator may terminate a study participant's participation in the study if:

- Any clinical adverse event (AE) or other medical condition or situation occurs such that continued participation in the study would not be in his/her best interest.
- The participant meets an exclusion criterion (either newly developed or not previously recognized) that precludes further study participation.

### **5.6.2 *Handling of Subject Withdrawals or Subject Discontinuation of Study Intervention***

If parent/caregiver informs the study staff that he/she does not wish to continue with the study any further, the staff member will document the reason(s) and remove the parent and child from the study. The participant will be encouraged to continue with regular dental examinations at the child's dental home, which could detect early signs of disease. A participant's withdrawal from this study will not influence his/her future relations with any of the study's collaborating institutions, including but not limited to LA County EHS, UCSF, UCLA, or the child's medical or dental care provider. Withdrawals will not be replaced. All study data provided before withdrawing will be used for analysis, unless the participant asks that her/his data and her/his child's data not be used.

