Among children who did not have a documented ChildPlus dental visit at baseline, parents/caregivers in the Fixed incentive group will be eligible for a \$40 reward if they take their child to a dental check-up visit and it is documented in the ChildPlus database by the 2-month follow-up visit. Among children without a ChildPlus documented baseline dental visit in the Drawing incentive group, parents/caregivers whose child has a documented ChildPlus dental visit by the 2-month follow-up will have a 10% chance of winning \$400 in a drawing.

The monetary incentive groups will be told that having a preventive dental visit will earn them an incentive equivalent to 4 weeks of toothbrushing. Thus, the total expected value

of exceeding the higher-adherence threshold throughout the intervention period is \$80 from toothbrushing and \$40 from dental visit attendance.

To claim any incentives, including for syncing data, a parent/caregiver and child must attend the 2-month follow-up visit. All payments will be awarded as gift cards at the 2-month visit, but 2-month follow-up visit questionnaires will determine if another modality would be preferred in the future Phase II/III stage. After returning the TP pump participants will be provided a new TP pump and two new brush heads at the end of the intervention.

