### **7.5 Withdrawal Visit**

No early termination or withdrawal visits are anticipated, but in the event that this occurs, such a visit would follow the same guidelines established for a final study visit as long as the parent/caregiver is willing.

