Descriptive statistics (means, standard deviations, frequencies, 95% confidence intervals) will be used to summarize the group specific findings. An intention-to-treat (as assigned) approach will be used. Group estimates and percent difference for parents/caregivers brushing children’s teeth, ChildPlus documented dental attendance, EHS staff participation, parent/caregiver participation (informed consent), willingness to be randomized, willingness to sync smart TB to app, acceptability of the smart powered TB, child willingness to cooperate with dental screening, extraoral photo and plaque assessment, willingness to bring the TP pump to the 2-month visit, item completion/missingness among the 3 groups will be estimated with standard errors and 95% confidence intervals (CIs) to provide valid and precise estimates for sample size calculations for the future Phase II/III trial. If data are not Normally distributed, Normalizing transformations or nonparametric methods will be used. Multiple imputation models will be used for missing data. Although this pilot is not primarily focused on testing for statistically significant differences among groups, analysis of covariance (or nonparametric analysis of covariance) adjusting for potential confounders will be used to estimate effect sizes of the two monetary reward groups versus the control non-monetary reward condition to be used in sample size calculations.

Toothbrushing measures (smart powered TB, parent/caregiver diaries), child plaque scores, TP usage (change in pump weight) will be compared with Pearson (or nonparametric Spearman) correlation coefficients to assess consistency in the various measures. Toothbrushing measures (smart powered TB, parent/caregiver diaries) will be examined overall and by group over time (2 months) to assess for possible temporal effects (e.g., short-term smart powered TB novelty effect). Validity of the TB measures will be assessed by evaluating concordance of: TB diaries with smartphone app TB data; TB diaries with DI plaque score; TB diaries with TP pump weight change; smartphone app TB data with DI plaque score; smartphone app TB data with TP pump weight change; and DI plaque score with TP pump weight change.

---

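### Section 5.6.2 gives a family ending active participation no way to leave passive ChildPlus collection open, so a dental outcome that could be read without a visit is left to imputation

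*Protocol*

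**What the plan says.** **Leaving the study.** Section 5.6.2 is titled "Handling of Subject Withdrawals or Subject Discontinuation of Study Intervention". Its rule applies when a parent tells staff that he or she "does not wish to continue with the study any further"; then "the staff member will document the reason(s) and remove the parent and child from the study". On data, "All study data provided before withdrawing will be used for analysis", unless the parent asks that they not be used. Withdrawn dyads are not replaced. The section gives no separate rule for discontinuing the intervention and does not mention ChildPlus.

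**The dental outcome.** Under sections 3.2.1 and 8.5 it is whether a child with no ChildPlus dental visit at baseline has one documented at follow-up. Section 16.2 obtains it by extraction from the EHS database. Section 3.2.1 lists parents' willingness to approve that access as a feasibility measure; section 5.1 does not make it an inclusion criterion.

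**Analysis and size.** Section 12.3 states: "An intention-to-treat (as assigned) approach will be used". It plans multiple imputation for missing data. Sections 4 and 12.2 set 12 dyads per arm, with no stated allowance for dropout.

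**Closing visit and payment.** If an early visit occurs and the parent is willing, section 7.5 says "such a visit would follow the same guidelines established for a final study visit". The final-visit steps in section 7.3 include handing over accumulated rewards. Section 6.2 says "To claim any incentives, including for syncing data, a parent/caregiver and child must attend the 2-month follow-up visit". Section 5.6.1 lets a parent decide "not to participate in the study further at any time without penalty".

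**The concern.** The heading promises two situations and the text handles one. A parent with a new job or child-care problem (reasons that section 5.6.1 itself foresees) may want no more visits, texts or brushing records, yet not mind the study reading a ChildPlus entry. As written, staff can only remove the dyad, and the data used stop there. One of the two behavioural primary measures is then missing for a child whose record could still be read.

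This matters because the arms are small, the dental measure uses only part of each arm, and section 12.3 chooses the arm for the future trial by comparing outcomes against a 20% margin. A few missing binary outcomes can matter at that scale.

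There is also a practical gap: staff cannot tell from the text whether a family that leaves early receives rewards already earned.

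**Working it through.** **Step 1. Is the outcome really obtainable without the family?** By sections 3.2.1, 8.5 and 16.2 it needs no visit, phone or brush, only database access and the parent's approval. A section 7.5 closing visit does not replace it, because a record read on that earlier day misses dental visits between then and the two-month date.

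**Step 2. Reproduce the protocol's own figures (section 12.2).**
- Half-width of a 95% CI, n = 12: 1.96 × √(p(1 − p)/n). At p = 0.5 this is 1.96 × √(0.25/12) = 0.283; at p = 0.032 it is 0.0996. The stated range is 0.100 to 0.283.
- Chi-square test, 3 × 12 = 36: noncentrality = N × V / (p̄(1 − p̄)) = 36 × 0.066 / (0.547 × 0.453) = 9.59 on 2 df, giving power 0.798. The stated power is 80%. This holds when V is the variance with divisor 3; the other convention gives about 61%.

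**Step 3. Effect of lost outcomes.** The protocol gives no withdrawal rate, so 1, 2 or 3 losses per arm are assumed. The last two columns give the distance between best and worst case for a binary outcome: lost/12 for one arm, and twice that for a difference between two arms.

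| Lost per arm | n | Half-width at 0.5 | Chi-square power | Range, one arm | Range, difference |
|---|---|---|---|---|---|
| 0 | 12 | 0.283 | 0.798 | 0 | 0 |
| 1 | 11 | 0.295 | 0.760 | 0.083 | 0.167 |
| 2 | 10 | 0.310 | 0.717 | 0.167 | 0.333 |
| 3 | 9 | 0.327 | 0.668 | 0.250 | 0.500 |

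If the 20% margin in section 12.3 means percentage points, two losses per arm already give a range (0.333) wider than the margin. The text does not say whether the margin is absolute or relative.

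**Step 4. The dental subset.** All 12 per arm is an upper limit, because only children without a baseline ChildPlus visit count. Assuming 9 such children per arm, the half-width at 0.5 goes from 0.327 with none lost to 0.346 and 0.370 with one and two lost. Assuming 6, it goes from 0.400 to 0.438 and 0.490.

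**Step 5. What imputation restores.** It keeps the child in the analysis but adds only what the observed covariates and earlier data predict about attendance. If they predict it weakly, Steps 3 and 4 are close to the real loss; if they predict it well, the loss is smaller. Reading the record avoids the question.

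**Step 6. Payment.** Visit 2 is at day 60 ± 28, that is, days 32 to 88. A closing visit on day 32 or later can be counted as Visit 2, where section 7.3 hands over rewards. Before day 32, section 7.5 taken with section 7.3 points to handing them over, while section 6.2 ties every claim to the two-month visit. The text does not settle which governs.

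**The case against.** The strongest defence is that the rule is triggered by a wish to leave the study, not by poor adherence, and that reading no records after a parent has left is a respectable view of voluntary withdrawal. Whether approval of ChildPlus access survives withdrawal depends on the consent form, which is kept separately and is not available here. Section 7.5 still offers a closing visit, data given earlier are kept, and imputation is planned. All of this stands, and it limits the point to families who would have agreed to passive collection had they been asked.

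Four stronger readings are tempting but unsupported:
- A reader might infer that any family that stops syncing is removed. It is not: section 6.2 only withholds that week's incentives, and the ChildPlus outcome is still collected.
- A reader might infer that section 12.3 is contradicted. Analysis as assigned concerns the arm in which a dyad is counted; section 5.6.2 fits poorly with its aim but does not contradict it.
- A reader might infer that early leavers forfeit their earnings, or that the payment rules flatly conflict. From day 32 a visit falls in the Visit 2 window; before then the text is ambiguous. Tying payment to Visit 2 is also a deliberate retention device.
- A reader might infer bias in a known direction. The protocol gives no basis for one, and families with low adherence can still collect the weekly $3 for syncing and the $30 for attending.

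**Conclusion.** The point holds in a limited form. Section 5.6.2 announces a rule for discontinuing the intervention and supplies none. Followed as written, it gives up a primary dental outcome that could still be read for families willing to allow it. No such loss need occur where permission stands; where it is revoked, the loss remains.

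The size is modest per child but not negligible in arms of 12. Under assumed losses of one to three per arm, the half-width grows by 0.012 to 0.044 (0.295 − 0.283 and 0.327 − 0.283) and chi-square power falls from 0.80 to between 0.76 and 0.67, with a greater effect on precision in the smaller dental subset. These figures rest on assumed withdrawal counts and subset sizes, count every loss as one that reading ChildPlus would have prevented, and take imputation as adding little. The missing route itself rests on the text alone. The payment question is a separate ambiguity, confined to withdrawal visits before day 32.

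**What to change.** In section 5.6.2 and the consent form, distinguish three decisions and record which one the parent makes:
1. stopping the brush, app, texts or incentive programme;
2. declining further visits;
3. withdrawing permission for data use.

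For the first two, extract ChildPlus at the planned two-month date for every randomised child whose parent approved access and has not revoked it, and analyse the result in the assigned arm. State that date once: section 3.2.1 speaks of three months for this outcome, while sections 6.2 and 8.5 speak of two.

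Separately, reconcile sections 5.6.1, 6.2, 7.3 and 7.5 so that staff and families know whether rewards already earned are handed over at a withdrawal visit before day 32. Which payment rule applies is for the investigators to decide.

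The cost is protocol and consent wording, with IRB review of the change, and one more question to a withdrawing parent. The extraction itself is already planned.

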## **5.7 Premature Termination or Suspension of Study**

This study may be suspended or prematurely terminated if there is sufficient reasonable cause. Written notification, documenting the reason for study suspension or termination, will be provided by the suspending or terminating party to [name] (PIs). If the study is prematurely terminated or suspended, the PIs will promptly inform the IRB and will provide the reason(s) for the termination or suspension.

Circumstances that may warrant termination include, but are not limited to:

- Determination of unexpected, significant, or unacceptable risk to subjects.
- Insufficient adherence to protocol requirements.
- Data that are not sufficiently complete and/or evaluable.
- Determination of futility.

---

## 6 STUDY INTERVENTION

### 6.1 Description of Behavioral Intervention

Child-parent/caregiver dyads will be assigned in a 1:1:1 ratio to one of three conditions: Control group, a Fixed monetary incentive condition, or a Drawing monetary incentive condition.

In the Control group, participants will not be eligible to receive any performance-based incentives during the first 2 months, but will receive information on their toothbrushing adherence per the smart powered TB data, as well as other informational reminders about oral health care behaviors. After the 2-month follow-up visit, the control group will have the ability to earn Fixed incentives in a delayed (waitlisted) 2-month open label extension. This is not a formal part of the UH2 study evaluation for the future trial preparation, but rather a necessary condition of the trial design to assure that all participating EHS parents/caregivers have the chance to earn the same monetary incentives. They will follow the same procedures (texting notifications) as the Fixed intervention group from the 2-month follow-up to a 4-month follow-up. At the 4-month follow-up visit, they will be able to collect the earned incentives. To receive the rewards the parent/caregiver and child must attend the 4-month visit and return their toothpaste pump. Participants will be provided a new TP pump and 1 new brush head.

In the Fixed monetary incentive group, participants will be eligible to earn one of two incentive amounts every week. They will earn \$5 in incentives if the participant meets a lower adherence threshold (i.e., likely 7 times brushing his/her child's teeth) during the preceding week. They will earn \$10 in rewards if the participant meets a higher adherence threshold (i.e., likely 14 times brushing his/her child's teeth) during the preceding week. The exact thresholds may be modified based on UH2 formative research information being collected prior to the trial.

In the Drawing monetary incentive group, participants will be sent a text message about entering into a drawing every week; the participant can reply to the text with a 2-digit number or let his or her number be chosen at random. Chances of the amount of winnings possible depend on the participant's level of adherence. A participant who meets the lower adherence threshold (i.e., same as in the Fixed monetary incentive group; e.g. 7/week) will be eligible for an 18% chance (matching one digit with the winning number) of winning \$25 and a 1% chance (matching both digits in order) of winning \$50 (an expected value of \$5). A participant who meets the higher adherence threshold (i.e., same as in the Fixed monetary incentive group; e.g. 14/week) will be eligible for a 34% chance (matching either digit without regard to order) of winning \$25 and a 4% chance (matching both digits without regard to order) of winning \$50 (an expected value of \$10). Participants who fail to reach either adherence threshold can send a reply text message to enter into the lower adherence drawing, and if chosen as a winner will receive a text message that states what

they would have won had they brushed more regularly, thereby taking advantage of a psychological tendency toward anticipated regret to motivate future brushing.

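### In Protocol 6.1 the higher-tier drawing's odds, matching rule and stated $10 value contradict each other: the printed odds are worth $10.50 a week, and no digit rule produces them

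*Protocol*

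**What the plan says.** Protocol section 6.1 sets the weekly toothbrushing incentives at two thresholds that are the same in both monetary arms.

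- **Fixed arm.** $5 at the lower threshold, and $10 "in rewards if the participant meets a higher adherence threshold".
- **Drawing arm, lower tier.** An "18% chance (matching one digit with the winning number) of winning" $25 and a "1% chance (matching both digits in order) of winning" $50, with a stated expected value of $5.
- **Drawing arm, higher tier.** The participant is "eligible for a 34% chance (matching either digit without regard to order) of winning" $25, with a "4% chance (matching both digits without regard to order) of winning" $50. The stated expected value is $10.
- **Ticket.** Each week "the participant can reply to the text with a 2-digit number or let his or her number be chosen at random". No number is excluded.

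Section 6.2 gives 8 paid weeks and a single expected total of $80 from toothbrushing at the higher threshold, plus $40 for a dental visit. Both monetary arms are told that the visit "will earn them an incentive equivalent to 4 weeks of toothbrushing". The visit incentive is $40 in the Fixed arm and a 10% chance of $400 in the Drawing arm.

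**The concern.** The prizes and odds printed for the higher tier do not multiply out to the value printed beside them. The two odds also look as if they come from two different matching rules, so a programmer could not build a draw that satisfies the paragraph as it stands.

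Equal value is part of the design. The thresholds are shared, the values are given as $5 and $10 in both arms, and section 6.2 gives one total for both. Section 2.1 motivates comparing incentive structures at the same cost. Section 5.5 asks that fairness be transparent to parents, to whom the rewards program is explained with teachback. Under section 12.3 the chosen arm goes forward to the Phase II/III trial, so an undefined draw could go forward with it.

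**Working it through.** **Inputs.** Odds, prizes and stated values from section 6.1; number of paid weeks, $80 total and visit incentive from section 6.2. One assumption is needed: tickets and winning numbers run from 00 to 99, all equally likely, since the protocol says only that the number has two digits.

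**1. Reproduce the figures that work.** Value = 25 × P(smaller prize) + 50 × P(larger prize), with the prizes mutually exclusive.
- Lower tier: 25 × 0.18 + 50 × 0.01 = $5.00, as stated.
- Dental visit: 0.10 × 400 = $40, as stated.
- The lower odds follow from matching by position: 2 × 0.1 × 0.9 = 18% and 0.1 × 0.1 = 1%. This supports the 00–99 format. With 10–99 the lower tier would be worth $5.28.

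**2. Apply the same convention to the higher tier.**
- 25 × 0.34 + 50 × 0.04 = 8.50 + 2.00 = $10.50, not $10.
- Over 8 weeks: 8 × 10.50 = $84, not $80.
- If the 34% is taken to include the 4%: 25 × 0.30 + 50 × 0.04 = $9.50, again not $10. That convention would also turn the lower tier into 25 × 0.17 + 50 × 0.01 = $4.75.

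**3. Can any digit rule give 34% and 4%?** For a ticket with two different digits, 8 × 8 = 64 of the 100 winning numbers contain neither digit, so at most 36 can win anything. For a repeated-digit ticket the figure is 100 − 9 × 9 = 19. The printed odds sum to 38%, which exceeds both limits.

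**4. What the plausible rules do give**, by enumerating every ticket against every winning number:

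| Meaning of matching both digits | Two different digits | Repeated digit | Average over random tickets |
|---|---|---|---|
| Same pair, in any order | 34% / 2% = $9.50 | 18% / 1% = $5.00 | 0.9 × 9.50 + 0.1 × 5.00 = $9.05 |
| Both winning digits appear on the ticket | 32% / 4% = $10.00 | 18% / 1% = $5.00 | 0.9 × 10.00 + 0.1 × 5.00 = $9.50 |

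The printed 34% belongs to the first row and the printed 4% to the second. A more strained third rule, that every ticket digit must occur in the winning number, gives 34%/2% for different digits and 0%/19% for a repeated digit, $9.50 in each case. It does not yield the printed pair either.

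**5. Repeated digits.** Under both tabulated rules, a ticket such as 77 is worth $5.00 at the higher threshold, the same as at the lower one. For that week, moving from 7 to 14 brushings adds nothing to the drawing's value.

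**6. Eight-week totals against $80.** Printed odds $84. Random tickets: 8 × 9.05 = $72.40 or 8 × 9.50 = $76.

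**The case against.** The strongest reply is that this is a slip of small consequence. On the printed odds the gap is $0.50 a week, at most $4 over 8 weeks against a stated total of $120. Chance in the draw is far larger: one week's winnings have variance 0.34 × 625 + 0.04 × 2500 − 10.50² = 202.25, so an 8-week total has an SD of about $40, and the mean of 12 participants has a standard error of about $11.6. The primary objective is feasibility and acceptability, section 12.2 does not size the pilot mainly for group comparisons, and section 12.3 lets the choice of arm rest partly on which is most appropriate. All of this stands, and nothing here shows that a 5% gap could change which arm is chosen.

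Three stronger readings are tempting, and the protocol does not support them.

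- **That the arms are unmatched in general.** The lower tier and the dental-visit incentive agree exactly. Only the higher tier is affected.
- **That the digit rule is worth $9.50 at most.** This holds only if matching both digits means the same pair in any order. The reading that yields the printed 4% for two different digits gives exactly $10.00, so 34% may be a slip for 32%. The text does not settle it.
- **That Drawing participants could be held to $40 over 8 weeks, or that the four-week message is plainly wrong.** The first needs a repeated-digit ticket every week, and a system that accepts such tickets and pays by literal matching. For the second, the printed odds make $40 worth 40 / 10.50 = 3.8 weeks.

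What the reply leaves untouched is that odds, rule and value cannot all be implemented together.

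**Conclusion.** The higher-tier paragraph of section 6.1 is wrong as written. That the printed odds are worth $10.50 and not $10 needs no assumption beyond the convention that reproduces the lower tier. The resulting mismatch with the Fixed arm is 5% at the higher tier only.

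That no digit rule yields both 34% and 4% rests on the 00–99 format. Which rule was intended is open, so the value for two different digits should be read as $9.50 to $10.00. The random-ticket averages of $9.05 and $9.50 also assume that repeated digits are allowed and paid by literal matching. A reader might infer that the fixed-versus-drawing comparison is materially confounded by incentive size; the figures do not show that. The case for correction is that these odds define the Drawing arm and its intended equality with the Fixed arm, and that the draw cannot be programmed as described.

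**What to change.** Before the SMS drawing is programmed, bring four items in section 6.1 into agreement: the odds, the matching rule, the handling of repeated digits and the expected value. Then check them against the $10 Fixed payment in the same section and the $80 total and four-week message in section 6.2.

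- **Option that keeps the prizes and the $10.** Define the $50 event as both winning digits appearing on the ticket (4%), change 34% to 32%, and accept or generate only tickets with two different digits. Then 25 × 0.32 + 50 × 0.04 = $10.00 a week and $80 over 8 weeks. Participants lose the choice of the 10 repeated-digit numbers.
- **Option that keeps the printed odds.** Restate the Drawing values as $10.50 and $84 and acknowledge that the arms differ by 5% at the higher tier. Winners would then have to be drawn by a mechanism other than the described digit match, which cannot deliver these odds.

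Other repairs are possible, and the protocol does not dictate one. The cost is a wording change in the protocol and participant messages, plus at most one validation rule in the SMS system under the first option. The second option also needs a redesigned draw.
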